## Abstract

**Introduction:**

Sleep health is an important part of health and has become a common concern of society. For anxiety insomnia, the commonly used clinical therapies have limitations. Alternative and complementary therapy is gradually rising and showing remarkable effect in clinical practice. This is the first study to evaluate the therapeutic effect of Taijiquan combined with acupoint pressing in the treatment of anxiety insomnia in college students and to compare the difference in intervention before and after sleep, to choose the best treatment time.

**Methods and analysis:**

This is a multicenter, single-blind, randomized controlled trial. A total of 126 eligible subjects who have passed the psychological evaluation and met inclusion criteria by completing a psychometric scale will be randomly divided into treatment group A (treat before sleep), treatment group B (treat after sleep) and control group C (waiting list group) in a ratio of 1:1:1. All the three groups will receive regular psychological counseling during the trial, and the treatment groups will practice 24-style Taijiquan and do meridian acupuncture at Baihui (DU20), Shenting (DU24), Yintang (EX-HN3), Shenmen (HT7) and Sanyinjiao (SP6). This RCT includes a 2-week baseline period, a 12-week intervention period, and a 12-week follow-up period. The main results will be measured by changes in the Pittsburgh sleep quality index (PSQI) and Hamilton anxiety scale (HAMA). The secondary results will be measured by the generalized anxiety scale (GAD-7) and insomnia severity index (ISI). The safety of the intervention will be evaluated at each assessment. The statistical analysis of data will be carried out by SPSSV.26.0 software.

**Discussion:**

We expect this trial to explore the effectiveness of Taijiquan combined with acupoint pressing in the treatment of anxiety insomnia in college students and choose the best treatment time by comparison.

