### Sample size

This study uses qualitative data group design sample size estimation formula:

$$n_{1}=n_{2}=\frac{\begin{array}{c} {}[z_{\alpha /2}\sqrt{P\,\left(1-P\right)\,\left(1+C\right)/C}\\ +z_{\beta }\sqrt{P_{1}\,\left(1-P_{1}\right)\,P_{2}\,\left(1-P_{2}\right)/C}]{}^{2} \end{array}}{{\left(P_{1}-P_{2}\right)}^{2}}$$

Among them, Zα/2 is the *Z*-value corresponding to the inspection level, Zβ is the *Z* value corresponding to the second type of error probability, *p* is the combined rate of two samples, and p1 and p2 are the two population rates, respectively, c is the ratio of the two sets of sample content, and the inspection level is specified as α = 0.05, test power 1-β = 0.9, c = 1, using a two-sided test, the clinical effective rate of insomnia treatment is calculated as an index. According to related research reports, p1 is 0.68, p2 is 0.92, and p is 0.80. Substituting the formula can get a total sample size of 114 cases (12). Considering possible withdrawal or loss to follow-up during research interventions, the sample size must be expanded to ensure the progress of the research. Therefore, the sample size is expanded by 10% on this basis, and the total sample size is for at least 126 cases.

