## Discussion

This trial is a randomized controlled clinical trial, which aims to evaluate the efficacy and safety of Taijiquan combined with acupoint pressing in the treatment of anxiety insomnia in college students and to determine the best intervention time for Taijiquan combined with acupoint pressing in the treatment of anxiety insomnia.

Studies have shown that practicing Taijiquan and acupoint pressing can reduce the symptoms of anxiety insomnia to some extent, but the effectiveness of the combination of Taijiquan and acupoint pressing in the treatment of anxiety insomnia is not clear (27, 28). This experiment will be conducted in multiple centers, using a randomized controlled trial to blind the trial evaluators and data statistical analysts to evaluate the effectiveness of Taijiquan combined with acupoint pressing in the treatment of anxiety insomnia in college students. By comparing different treatment times of Taijiquan and acupoint pressing, we can find the best time for the treatment of anxiety insomnia. In addition, this study designed according to the Comprehensive reporting Test Standard (CONSORT) statement and guidelines will provide effective evidence for guiding the clinical practice of Taijiquan combined with acupoint pressing in the treatment of anxiety insomnia.

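### Choosing the best treatment time is a stated aim, but the A versus B comparison is not sized, and about 38 to 42 per arm cannot reliably separate the two times

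*Protocol article*

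**What the plan says.** Treatment time is an aim throughout the protocol article. The Abstract (Introduction) announces a comparison of the intervention before and after sleep so that the better time can be selected. The Abstract (Discussion) says the trial will "choose the best treatment time by comparison". The last paragraph of Background puts timing within the main purpose, Study design repeats it, and the Discussion says that by comparing times "we can find the best time for the treatment of anxiety insomnia".

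The Sample size section defines its terms for two groups: "p1 and p2 are the two population rates, respectively, c is the ratio of the two sets of sample content". The design values are "the inspection level is specified as α = 0.05, test power 1-β = 0.9, c = 1, using a two-sided test". The endpoint is a binary one ("the clinical effective rate of insomnia treatment is calculated as an index"), and the rates are "p1 is 0.68, p2 is 0.92, and p is 0.80". The result is "Substituting the formula can get a total sample size of 114 cases", and then "the sample size is expanded by 10% on this basis, and the total sample size is for at least 126 cases". The two groups are not named, and no A versus B difference appears. The Abstract and Study design allocate the total 1:1:1 to A, B and the waiting-list group C.

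Statistical analysis provides analysis of variance and covariance for measurement data, CMH for counts, an intention-to-treat full analysis set as the main set, and a general threshold of p < 0.05.

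**The concern.** A and B receive the same procedures at different times of day, and the article commits itself to selecting one of the times. A selection needs enough information to separate the two arms. The only effect for which the trial is sized is one 24-point contrast between two unnamed groups, and the total from that calculation has to serve three arms.

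What is at stake is the timing conclusion. If the A versus B estimate is imprecise, a real difference will usually not reach significance. A non-significant result may then be reported as the two times being equally good, or the arm with the better observed mean may be recommended because the stated aim requires a choice.

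**Working it through.** **1. The plan's own figure.** Inputs from Sample size: two-sided α = 0.05 (z = 1.960), power 0.90 (z = 1.282), c = 1, p1 = 0.68, p2 = 0.92, p = 0.80. The standard formula is

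n = [1.960·√(2·0.80·0.20) + 1.282·√(0.68·0.32 + 0.92·0.08)]² / 0.24²

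= (1.1087 + 0.6916)² / 0.0576 = 3.241 / 0.0576 = 56.27, so 57 per group.

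Two groups give 2 × 57 = 114, the stated total. Three groups would give 171. With 10% added, 114 × 1.10 = 125.4, so 126. The total of 114 is therefore a two-group total. (As printed, the formula multiplies the two variance terms where the standard one adds them. That version gives 28.04, so 29 per group, which is 58 for two groups or 87 for three. Neither matches 114, so the additive form was evidently used.)

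**2. Size per arm.** 114 / 3 = 38 evaluable; 126 / 3 = 42 randomised. Both are carried below, because the main analysis set includes withdrawals.

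**3. Power for the planned contrast.** Power = Φ{[0.24·√n − 1.960·√0.32] / √0.2912}.

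- n = 38: Φ(0.687) = 75.4%
- n = 42: Φ(0.828) = 79.6%
- n = 57: 90.4%

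**4. Precision of A minus B.** In SD units the standard error is √(2/n), so the 95% half-width is 1.96·√(2/n).

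- n = 38: 1.96 × 0.2294 = 0.45 SD
- n = 42: 1.96 × 0.2182 = 0.43 SD

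Baseline adjustment at an assumed correlation of 0.5 multiplies these by √(1 − 0.25) = 0.866, giving 0.39 and 0.37 SD.

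**5. Power for A versus B.** The article gives no timing difference, so the values below are assumptions. Continuous outcomes use a two-sample t-test at 0.05 without baseline adjustment; rates use the two-proportion formula.

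| Assumed A–B difference | 38 per arm | 42 per arm |
|---|---|---|
| 0.2 SD | 14% | 15% |
| 0.3 SD | 25% | 27% |
| 0.92 vs 0.82 | 25% | 27% |
| 0.92 vs 0.77 | 44% | 47.5% |

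The difference detectable with 80% power is (1.960 + 0.842)·√(2/n) = 0.64 SD (n = 38) or 0.61 SD (n = 42).

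**6. Picking the arm with the better observed mean.** With a true gap of 0.2 SD, the wrong arm ranks first with probability Φ(−0.2/√(2/n)).

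- n = 38: Φ(−0.872) = 19%
- n = 42: Φ(−0.917) = 18%

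**The case against.** The strongest reply is that the comparison is not left open. The Abstract (Introduction) describes a direct comparison of the two times, and Statistical analysis supplies ANOVA, ANCOVA, the analysis sets and p < 0.05. The exact contrast, visit and order of scales are commonly left to a statistical analysis plan, which may exist and is not shown here. That stands, and the absence of those details is not the point.

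Four stronger readings are tempting, and the document supports none of them.

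- A reader might infer that nothing governs the A versus B comparison. The general methods and threshold just listed do apply to it.
- A reader might infer that a best time would be declared largely by chance. With a single direct test at 0.05, a false declaration occurs in 5% of trials. The 18–19% in step 6 applies only to ranking by observed means, a rule the article does not state.
- A reader might infer that timing will be judged by whether A, but not B, is significant against C. No passage proposes this.
- A reader might call a large A versus B difference implausible. The Discussion expects effects to vary with intervention time and gives no size, so the document neither supports nor excludes a large gap.

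It is also fair that the Abstract's wording is partly exploratory. None of this answers the sizing: the sample size basis and the wording of the aim are both printed, and they do not fit together.

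**Conclusion.** The point holds in this limited form. The article commits itself to a selection that its sample size was not built to make and cannot make reliably. The per-pair power of 90% is not met for any pair of arms, even at the assumed 24-point gap, where it is about 75–80%. For timing, the trial would usually miss differences of 0.2 to 0.3 SD, and an interval reaching about 0.43 to 0.45 SD either side of the estimate cannot show that the two times are equal.

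The shortfall in the planned power and the CI half-width follow from the article's own figures and 1:1:1 allocation (the half-width in SD units, before baseline adjustment). The A versus B power figures rest on assumed differences. If the true gap were about 0.6 SD or more, the trial would have roughly 80% power or better to detect it. The change is worth making because it is cheap and alters what the trial may conclude about timing.

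**What to change.** 1. Base the timing conclusion on the direct, baseline-adjusted A minus B difference, reported with its 95% CI. Name a better time only if that interval excludes zero. Otherwise report the question as unresolved, not as equivalence.
2. Label the comparison exploratory and state its expected precision: about ±0.43 to 0.45 SD, somewhat narrower after baseline adjustment.
3. In the Abstract, Background, Study design and Discussion, replace the language of choosing or finding the best time with estimating the difference between treatment times.
4. In Sample size, state that 114 is a two-group total and restate the power per pair of arms as about 75–80% for 0.68 versus 0.92.

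The cost is wording only, with no change to recruitment, visits or treatment. The downside is a less ambitious stated objective. Keeping 90% per pair instead would need 3 × 57 = 171 evaluable participants, or 189 to 190 with the 10% allowance (171 × 1.10 = 188.1; 171 / 0.9 = 190). Even that covers only a 24-point gap: 90% power for an assumed 0.3 SD timing difference needs about 234 per arm.

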**Clinical trial registration:**

[www.ClinicalTrials.gov], identifier [ChiCTR2200057003].

## Background

Anxiety insomnia is one of the most common clinical insomnia types of contemporary young college students. It is a mood disorder with a high incidence of relapse and a long course of the disease (1). College students are often affected by many external pressure factors such as academic performance, interpersonal communication, and social employment, resulting in bad emotions such as anxiety and irritability. If there is no timely effective intervention, they will begin to have symptoms of waking up repeatedly or severe difficulty in falling asleep and get progressively worse. If things go on like this, it will develop into anxiety insomnia (2). Relevant investigation results show that 18.3∼36.6% of college students have sleep quality problems or even sleep disorders, which seriously affect the quality of their study and life (3). Sleep health is an important part of physical and mental health and has become a common concern in society.

Modern studies show that Taijiquan can properly improve the system functions of the body, regulate emotions and relieve fatigue, and can improve the sleep quality of practitioners when the intensity of training is certain (4). The 24-style Taijiquan is selected and used in this study. The 24-style Taijiquan is based on Yang’s Taijiquan and has been compiled. Compared with traditional Taijiquan, it is more refined and standardized, and it fully reflects the characteristics of Taijiquan movement and meets the standard of harmony and unity (5). In the view of Traditional Chinese Medicine, insomnia is mainly caused by the disharmony of Yin and Yang, the imbalance of Ying and Wei, and the disorder of Zang-Fu viscera. The 24-style Taijiquan is influenced by traditional philosophy and contains the theory of balance of yin and yang, reflecting the Chinese culture’s philosophy of the unity of heaven and man and the Tao of nature, which has the effect of harmonizing yin and yang and unblocking meridians, while regulating the idea of balance and exercising the brain’s perception and control precision of the body (6–8). Acupoint pressing is a therapeutic method with meridians and acupoints as the core, combined with massage manipulation. Using the theory of meridians and acupoints to treat insomnia has a long history and its advantages (9). Clinical research results show that Baihui (DU20), Shenting (DU24), Yintang (EX-HN3), Shenmen (HT7), and Sanyinjiao (SP6) are common acupoints for insomnia treatment (10, 11).

For anxiety insomnia, oral drugs and psychological counseling are mostly used in clinical treatment at present. But the drugs have side effects such as addiction and drug resistance, while psychological counseling also has certain limitations. The therapeutic effect of this kind of disease still needs to be improved in clinical research. With the improvement of the modern medical levels, alternative and complementary therapy is gradually rising and showing remarkable effect in clinical practice. The main purpose of this RCT is to evaluate the clinical therapeutic effect of Taijiquan combined with acupoint pressing for college students with anxiety insomnia and to optimize the best treatment time. The results of the study will also provide evidence for the therapeutic effect of traditional exercise therapy and external acupoint therapy in treating anxiety insomnia.

## Methods

### Study design

This proposed study is a multi-centered, single-blinded, randomized non-pharmacological therapy trial with the assessor and statistician blinded to treatment allocation, evaluating the effect of Taijiquan combined with acupoint pressing in the treatment of college students with anxiety insomnia, and finding the best treatment time (12). The research team will include patients with anxiety insomnia according to the international diagnostic criteria DSM-5 (13). A total of 126 participants who have passed the professional psychological assessment will be enrolled in this trial from the universities in Chengdu, Sichuan Province. They will be randomly divided into treatment group A (treat before sleep), treatment group B (treat after sleep), and control group C (waiting list group) in the ratio of 1:1:1. The whole treatment process will be completed under the guidance of professional doctors and teachers of Chengdu University of Traditional Chinese Medicine in Sichuan, China. This test will be reported following the Comprehensive reporting Test Standard (CONSORT) statement (14). The flow chart of the trial is shown in Figure 1, and the schedule for registration, intervention, and evaluation is shown in Figure 2.

**FIGURE 1 F1:**
[figure not shown]
Flowchart of the study design.

**FIGURE 2 F2:**
[figure not shown]
Standard protocol items. PSQI, Pittsburgh sleep quality index; HAMA, Hamilton Anxiety Scale; GAD-7, Generalized Anxiety Disorder; ISI, Insomnia Severity Index.

### Participants recruitment

There will be three strategies for the recruitment of subjects in this trial. First, participants will be recruited from Chengdu University of Traditional Chinese Medicine. The second is to recruit on the campuses of Sichuan University, University of Electronic Science and Technology, Southwest University of Finance and Economics, Sichuan Agricultural University, and Southwest Jiaotong University and release recruitment information through offline lectures in the teaching building, WeChat, or other online platforms. Third, the information recruitment will be publicly published on the volunteer research platform of the subjects. During the recruitment process, the members of the research team must first introduce the specific research process such as the research periods, intervention methods, and trial groups to the subjects. The subjects must be randomly assigned and abide by the trial arrangements of each group. Researchers invite eligible subjects to join the study and sign an informed consent form and then conduct a baseline assessment. This trial will include 126 subjects according to the diagnostic criteria.

### Inclusion criteria

(1)Adult college students over the age of 18;(2)Insomnia is diagnosed according to the guidelines for the diagnosis and treatment of insomnia in Chinese adults, and the Pittsburgh sleep quality index (PSQI) score is ≥ 7;(3)According to the classification and diagnostic criteria of The Diagnostic and Statistical Manual of Mental Disorders (DSM), there is no severe depression and suicidal tendency, and the score on the Hamilton anxiety scale (HAMA) is ≥ 14;(4)No treatment-related to insomnia or anxiety symptoms in the last 3 months;(5)Have certain learning ability, be able to practice 24-style Taijiquan independently, find the designated meridians, and complete acupoint pressing;(6)Voluntarily participate in the experimental study and sign the informed consent and confidentiality letter.

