### Exclusion criteria

(1)Meet the classification and diagnostic criteria of The Diagnostic and Statistical Manual of Mental Disorders (DSM) for severe emotional and mental disorders;(2)Have a history of severe dependence on psychotropic drugs and sleep drugs;(3)Have a history of serious diseases of important organs (heart, liver, and kidney) or some sudden acute diseases;(4)Pregnant and lactating women;(5)Have more serious bad habits affecting sleep, such as smoking, drinking, and Internet addiction;(6)Recent major emotional trauma;(7)Any other circumstances that the researchers believe may make the patient unable to complete, comply with, or unsuitable for this study.

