### Interventions

The treatment groups will practice 24-style Taijiquan under the guidance of professional teachers. The training time is 15 min each time, once a day, for 12 weeks. The essentials of Taijiquan movements are based on the 24-style simplified Taijiquan compiled by the State Sports Commission (now the State Sports General Administration) in 1956 as the standard. The treatment groups will also carry out acupoint pressing training in the acupuncture and massage laboratory of Chengdu university of traditional Chinese medicine, mainly training Baihui (DU20), Shenting (DU24), Yintang (EX-HN3), Shenmen (HT7), and Sanyinjiao (SP6) acupoint positioning and thumb pressing and kneading techniques (17), while the pressing and kneading are required. Generally, pressing for about 1 min. It is appropriate that the patient feels obvious pain at the acupoints and can bear it. Participants will press the above five acupoints once or twice during the test time, and then change one acupoint for 1–2 min and then change one acupoint for a total of about 15 min. The subjects in the treatment group will receive compound treatment for 12 weeks, once a day for 30 min, including 15 min of 24-style Taijiquan and 15 min of acupoint pressing. To maintain the standard of the operation of the experiment, the subjects will practice for 3 days before the intervention, and after the movement is standardized, they will be trained every 2 weeks in Taiji Avenue and acupuncture and massage laboratory of Chengdu University of Traditional Chinese Medicine to avoid forgetting movements. The research team will assess the subjects on 24-style Taijiquan (a score of 60 or above is considered a pass) and if they fail they will be given additional training until they meet the assessment standard. See Table 1 for details of the scoring scale.

**TABLE 1 T1:** Taijiquan mastery rating scale.

Scoring items	Scoring criteria
Hand shapes, maneuvers, steps, footwork, legwork	2 points for each minor error; 3 points for each significant error; 5 points for each serious error; 6–10 points for multiple errors in one movement.
Smooth and precise force points consistent, rounded and coordinated movements	1–3 marks will be deducted for minor deviations from the requirements, 4–6 marks for significant deviations and 7–10 marks for serious deviations.

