Natural, focused awareness appropriate speed and outstanding style	1–3 marks will be deducted for minor deviations from the requirements, 4–6 marks for significant deviations and 7–10 marks for serious deviations.
Forgetting the action	3–5 marks will be deducted for each instance of forgetfulness, depending on the degree.
Out of balance	1 point for each wobble; 2 points for each support; 3 points for successive supports.
Number of movements	3 marks will be deducted for each extra or missing movement.
Direction of movement	One point for each deviation of 45° or more from the prescribed direction.
Repeat the set	If the examination is interrupted due to forgetfulness or mistakes, the examination may be repealed once and 10 points deducted, and so on.
Unfinished sets	Those who do not complete the routine will not be graded and will be marked as failing.

A total of 100 points will be awarded, with a total score of less than 60 being unqualified.

Group A receives combined treatment 30 min before sleep. First, 24-style Taijiquan training will be performed for 15 min each time, once a day. Then do acupoint pressing at Baihui (DU20), Shenting (DU24), Yintang (EX-HN3), Shenmen (HT7), and Sanyinjiao (SP6), kneading 1∼2 times for 1∼2 min. And then replacing with the next acupoint, each acupoint will be kneaded 1∼2 back and forth, a total of 15 min of continuous pressing. After each treatment, study members should make strict records to ensure the full participation of subjects in the study (18). Group B does the therapy of Taijiquan combined with acupoint pressing 30 min after waking up, and the treatment procedures and methods are the same as those of Group A. Group C will not accept any intervention on Taijiquan or acupoint pressing, and maintain their normal lifestyle. After the study, subjects in this group can choose to participate in the treatment of 24-style Taijiquan training combined with acupoint massage.

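### Inclusion criterion 5 is worded as an existing skill in the trial intervention, and no exclusion keeps out students who already practise it regularly, so habitual practitioners can enter every arm

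*Protocol article*

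**What the plan says.** All references are to the protocol article.

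- **Inclusion criteria, item 5:** entrants must "Have certain learning ability, be able to practice 24-style Taijiquan independently, find the designated meridians, and complete acupoint pressing".
- **Inclusion criteria, item 4:** the only washout is "No treatment-related to insomnia or anxiety symptoms in the last 3 months".
- **Exclusion criteria:** there are seven items. None mentions current or past Taijiquan or self-acupressure. The nearest is a catch-all left to judgement: "Any other circumstances that the researchers believe may make the patient unable to complete, comply with, or unsuitable for this study".
- **Randomization and blinding:** allocation follows the baseline assessment and the confirmation of eligibility.
- **Interventions:** instruction in the Taijiquan set, point location and pressing technique is described for the treatment groups. For them, "the subjects will practice for 3 days before the intervention", with refresher sessions every 2 weeks and a pass mark of 60. For the controls, "Group C will not accept any intervention on Taijiquan or acupoint pressing, and maintain their normal lifestyle"; they may take up the programme only after the study.
- **Participants recruitment:** "First, participants will be recruited from Chengdu University of Traditional Chinese Medicine". Five other universities and a public volunteer platform follow.

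**The concern.** Criterion 5 is a gate before randomisation, but it is phrased as a skill that the trial itself supplies after randomisation and withholds from group C. Recruiters on several campuses could apply it differently: some as ability to learn, others as ability already held. Under either reading, a student who already does Taijiquan or self-acupressure regularly passes, and nothing else in the eligibility lists stops that student.

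Two contrasts are at stake. The first is treatment against waiting list: a practitioner assigned to A or B receives less that is new. The second is A against B, which the protocol names as a main purpose (the best treatment time). A practitioner assigned to one time of day may keep an existing habit at the other, so the assigned time no longer describes what was done.

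Group C adds an ambiguity of its own. For a habitual practitioner, taking no Taijiquan or acupressure and keeping a normal lifestyle are different instructions.

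**Working it through.** **1. Sequence of the passages**

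| Step | What the protocol provides | Who receives it |
|---|---|---|
| Eligibility | Criterion 5: able to practise the set independently, find the points and complete the pressing | All entrants |
| Baseline, then allocation | Scales, then 1:1:1 randomisation | All entrants |
| Training | 3 days of practice, technique teaching, pass mark, refreshers | A and B only |
| Training after the study | Optional | C |

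As worded, the first step asks for what the third step delivers.

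**2. Can a regular practitioner be kept out?**

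- Criterion 4 removes someone who used either technique as treatment for insomnia or anxiety in the last 3 months. It does not reach someone who does Taijiquan as exercise or habit.
- Exclusions 1 to 6 concern psychiatric disorder, drug dependence, organ or acute disease, pregnancy and lactation, harmful habits, and recent trauma. None applies.
- Exclusion 7 is discretionary and turns on inability to complete or comply, or on unsuitability. Under criterion 5 a skilled practitioner looks well suited.

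So nothing definite keeps the practitioner out.

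**3. Where the contrast weakens**

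- *A or B:* less new exposure, so less expected change from baseline, and possible practice at the other time of day.
- *C, habit continued:* the effect of a stable habit is already in the baseline score, so continuing it does not by itself produce new improvement.
- *C, habit stopped:* the control condition becomes withdrawal of a habit and no longer usual life. The sentence on group C does not settle which applies.

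**4. Illustration of size**

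The plan's own figure comes first. Inputs from Sample size: "α = 0.05, test power 1-β = 0.9, c = 1, using a two-sided test"; "p1 is 0.68, p2 is 0.92, and p is 0.80". With the standard formula (sum of the two variances under the second root):

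n = [1.96 × √(2 × 0.80 × 0.20) + 1.2816 × √(0.68 × 0.32 + 0.92 × 0.08)]² / 0.24²
= (1.1087 + 0.6916)² / 0.0576 = 56.3, rounded up to 57 per group.

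57 × 2 = 114, which matches the plan. 114 × 1.10 = 125.4, rounded up to 126, which also matches.

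Assume that a share f of entrants already practises and gains nothing from assignment. The treated rate is then 0.92 − 0.24f, the control rate stays at 0.68, and the difference is 0.24 × (1 − f). With p̄ the mean of the two rates, power at n = 57 is

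Φ{[d√n − 1.96√(2p̄(1 − p̄))] / √(p₁(1 − p₁) + p₂(1 − p₂))}.

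| f (assumed) | Treated rate | Difference | Power, 57 per group |
|---|---|---|---|
| 0 | 0.920 | 0.240 | 90.4% |
| 5% | 0.908 | 0.228 | 86.3% |
| 10% | 0.896 | 0.216 | 81.4% |
| 20% | 0.872 | 0.192 | 69.6% |
| 30% | 0.848 | 0.168 | 56.2% |

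If practitioners keep a fraction g of the gain, the difference is 0.24 × [1 − f(1 − g)]. With f = 30% and g = 0.5 it is 0.24 × 0.85 = 0.204. The table (g = 0) is therefore the upper bound on dilution for each f.

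Both f and g are assumptions. The 0.24 is a difference in clinical effective rate, whereas the primary outcomes are PSQI and HAMA. The 57 is the two-group planning figure, not the arm size here. The table shows direction and sensitivity; it does not estimate the loss in this trial. No planning figure exists for A against B, so that contrast cannot be illustrated in the same way.

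**The case against.** The strongest reply is that criterion 5 opens with learning ability, and that three days of practice, a pass mark, retraining after failure and two-weekly refreshers would make little sense if mastery were required at entry. This stands. A reader might infer that the criterion screens out novices, but the training programme shows that novices are expected. What remains is that the rest of the clause says something else and should be brought into line.

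A second reply concerns group C. A reader might infer that practising controls receive the test treatment and so improve as the treated do. The documents do not support that. The Abstract defines the main results as changes in PSQI and HAMA, baseline is taken before randomisation, and such a student met PSQI ≥ 7 and HAMA ≥ 14 while practising. Dilution therefore comes mainly from A and B. By the same logic, calling these entrants non-responders is conjecture, and the point does not need it.

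Third, group C is barred from the intervention, and subjects must abide by the arrangements of their group. This helps, but the bar is on an intervention, and the same sentence tells the student to live as usual.

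Fourth, no habitual practitioner is shown to exist, and randomisation would spread any across the arms. That is fair: the effect would be conservative, not a bias in favour of treatment. The university of traditional Chinese medicine is one of six named, and the documents do not say how many of its students practise.

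Finally, recording outside practice is case report form content, which an article commonly leaves to the full protocol. Its absence is not part of this point. The eligibility criteria are printed as numbered lists, so their wording can be judged.

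**Conclusion.** The point holds as a wording and eligibility gap. Criterion 5 asks before randomisation for a skill that is taught afterwards to two arms only. No definite rule keeps out students who already practise regularly. The group C sentence gives a habitual practitioner two conflicting instructions. Such entrants would weaken the treatment-control contrast, mainly through smaller gains in A and B, and could blur A against B by practising at the other time of day.

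The size is unknown because the share of practitioners is not given. A reader might take the fall from 0.24 to between 0.216 and 0.168 (f of 10% to 30%) as the expected loss. It is not: it rests on an assumed share and on practitioners gaining nothing at all. If few or no practitioners enrol, the effect is negligible. This is a cheap improvement and does not invalidate the design.

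**What to change.** 1. **Criterion 5:** reword as ability to learn, and then perform independently after training, 24-style Taijiquan and self-acupressure.
2. **Exclusion criteria:** add regular practice of Taijiquan or self-acupressure within the last 3 months, the window already used in criterion 4. Extending this to all similar mind-body exercise would be a matter of preference and is not needed here.
3. **Interventions, group C:** reconcile the two halves of the sentence so that it gives one instruction on practice outside the trial. Which instruction applies is for the investigators to decide.

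The cost is an amendment to one inclusion criterion, one added exclusion and one clarified sentence. The downside is a slightly smaller recruitment pool, perhaps most noticeable at the first-listed university. The sample size and the analysis need no change on this account.
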